## Abstract

**Background:**

While there are indications of declining HIV infection rates in the general population globally, Tanzania included, men who have sex with men (MSM), female sex workers (FSW) and people who inject drugs (PWID), now called Key Populations (KP) for HIV epidemic have 2–20 times higher infections rates and contributes up to 30% of new HIV infection. Tanzania have developed a Comprehensive Guideline for HIV prevention among key population (CHIP) to address the epidemic among KPs. However, these populations are stigmatized and discriminated calling for innovative approaches to improve access to CHIP. This project seeks to test the effectiveness of healthcare workers and peer-to-peer engagement in promoting access to CHIP among HIV at risk populations in Tanzania.

**Methods:**

A quasi-experimental design involving Dar es Salaam City as an intervention region and Tanga as a control region will be done. Using respondent driven sampling, 1800 at risk population (900 from Intervention site and 900 from control site) will be recruited at baseline to identify pull and push factors for health services access. Stakeholder’s consultation will be done to improve training contents for CHIP among health care workers and peers. Effectiveness of healthcare workers training and peer engagement will be tested using a quasi-experimental design.

**Discussion:**

The results are expected to co-create service provision and improve access to services among KPs as a human right, reverse HIV infection rates among KPs and the general population, and improve social and economic wellbeing of Tanzanian.

**Trial registration:**

Retrospectively registered on 28th August, 2019 with International Standard Randomized Clinical Trial Number (ISRCTN11126469).

## Background

To date, HIV prevention and research in Africa has mainly focused on HIV transmission in the general population. Remarkably little attention has been paid to other population subgroups; and most notably to some of the groups that are now referred to by UNAIDS [1] as *key populations* at risk for HIV (KP). The sparse results from a limited number of studies on KP in sub-Saharan Africa suggest that HIV rates in men who have sex with men (MSM), people who inject drugs (PWID) and female sex workers (FSW) are 2 to 20 times higher as compared to the HIV rates in the general population [2–15]. Sexual relationship between individuals from KP and the general population are very common and these relationships may play a significant role in HIV transmission between the different groups [3, 5, 10, 14]. Access to health services is key in equipping these populations with the necessary tool for prevention, care and treatment. Although access to health services is a human right issue, results from previous studies indicate that access to services is grossly limited among KP due to stigma and discrimination, and due to poor attitudes towards most key populations in the population and health facilities and the illegal nature of their practices [16–19]. The results of a recent quantitative study among MSM in Tanzania, carried out by authors of this protocol indicated that, while access to services is a human right, only 32.2% of men with anal related disease utilized health facilities. About 73.2% of the respondents reported being stigmatized or discriminated when seeking services in public health facilities [3, 20]. Results of a recent integrated bio-behavioral survey, which involved 620 Tanzanian PWIDS, showed that, 90% of the PWIDS who tested HIV positive were unaware of their HIV status indicating a serious lack of prior access to services [4]. Since KP is estimated to account for about 30% of all new HIV infections in Sub-Saharan Africa, it is obvious that sustainable development goal number 3, UNAIDS goal of eliminating HIV epidemic as a public health threat by 2030 will not be realized if these population sub-groups lack access to prevention, care and treatment [6, 14, 15]. In order to fulfil these goals, UNAIDS have developed a consolidated guideline for HIV prevention, diagnosis, care and treatment among KP [21] and this guideline have been adopted in several countries. In December 2014, Ministry of Health, Community Development, Gender, Elderly and Children in Tanzania released an adapted Comprehensive Guideline for HIV prevention among KP (CHIP) which describes three important areas of interventions for KP (prevention activities, treatment and care activities and psychosocial support activities) [22]. However, there is presently no evidence on the best approaches to optimize access to CHIP among HIV at risk populations. Recent studies indicate that co-creation of health service provision through client engagement is effective in promoting communication with health system, access to services and user satisfaction [23, 24]. This approach is one of the primary goal of the WHO 2020 health program for empowerment of clients to achieve better service utilization and cost effectiveness [25]. Evidence on the extent to which KP and health care worker’s engagement to co-create KP-friendly services for KP is limited in Africa and urgent need to inform CHIP scale up.

### Objective

The overall objective of this project is to evaluate the effectiveness of healthcare workers and KP peer engagement in promoting access to CHIP among HIV at risk populations in Tanzania.

The project seeks to test the following hypotheses:
An interplay between individual, interpersonal, contextual, structural, and sociocultural and health system factors will influence health service access among KPCo-creation of health service provision through health care workers training and KP peers engagement is effective in improving access to CHIPs for HIV at risk population

## Methods

### Study setting

The study will be conducted in Dar es Salaam (intervention region) and Tanga Region (Control region). The selected regions are based on the results from previous studies which indicate the presence of substantial number of KPs in those regions with high HIV infection rates and limited access to health services [8, 20].

### Trial design

This is a quasi-experimental design with involvement of two parallel groups of KP living in Dar es Salaam (intervention region) and those living in Tanga region (control region). Co-creation of KP friendly services through training of health care workers and engagement of KP peers form the intervention component to be evaluated.

### Study population and eligibility criteria

The study will involve MSM (a man who regularly or occasionally has sex with another man), FSW (a woman who exchange sex for goods or money) and PWIDs aged 18 and above residing in the selected regions (Table 1).

**Table 1 Tab1:** Participants Inclusion and Exclusion Criteria

Population	Inclusion criteria	Exclusion criteria
Men who have sex with men	1. Have regular of occasional sexual prelateship with other men (man) 2. Had sex with a man during past 3 months 3. Aged 18 and above	1. Refuse to provide informed consent 2. Mentally ill or severely ill 3. Not a resident of participating region (have an address and lived in the region during the past 6 months)
Female sex workers	1. Exchange sex for goods or money 2. Have exchanged sex for goods or money during past 3 months 3. Aged 18 and above	1. Refuse to provide informed consent 2. Mentally ill or severely ill 3. Not a resident of participating region (have an address and lived in the region during the past 6 months)
People who inject drugs	1. Inject illicit drugs 2. Have injected drugs during past 3 months 3. Aged 18 and above	1. Refuse to provide informed consent 2. Mentally ill or severely ill 3. Not a resident of participating region (have an address and lived in the region during the past 6 months)

### Intervention

#### Peer education

A group of peers will be recruited from the members of the KP communities and trained on safe sexual behaviors, behavioral change communication and role modeling. They will be working within already established KP groups in the regions to offer education on the practice of safer sexual behaviors. They will serve as peer mentors in facilitating access to services and linking member of the KP to friendly clinics and services. This modality will deliver HIV intervention activities and care and treatment referral and support as part of the component of CHIP.

#### KP friendly services

KP friendly health professionals (nurses or clinical officer) will be trained in the selected nearby health facilities to serve as a gateway for KPs in the participating regions. Two such persons will be trained in each of the four selected facilities in Dar es Salaam to serve as a gateway to health services for KPs and will be facilitating service delivery to KPs. They will also be responsible for educating other health personnel in the respective facility and facilitate reduction in stigma and discrimination.

### Outcomes

The primary outcome of this study is change in the proportion of KP who report to have accessed health services measured at baseline, 12 months and 24 months following the intervention. (This correspond to months 36 and 48 of the study) when comparing intervention and control region. Secondary outcomes of the intervention include increased practice of safer sexual behavior (measured by increase in the proportion of participants reporting condom use during last sex and decrease in the proportion of participants reporting having sex with 2 or more sexual partners during past 12 months). Cost-effectiveness of the combined interventions will be assessed by incremental cost effectiveness ratio (ratio of change in the cost of CHIP provision by change in the proportion of population accessing health services. Data from KP interviews and health facilities cost records including those related to health care worker and preventive commodities such as condoms shall be collected.

### Participants recruitment timelines

The study will involve three phases where baseline data collection will take place in year 1 (first 12 months). Intervention mapping activities which will include health facilities, health care workers and KP peer selection, development of KP friendly training materials will be done during year 2. As part of client engagement, all training materials will be developed in collaboration with KP and health care workers and discussed in the community advisory board involving KP. Intervention implementation will take place during month 24 to month 48 with follow up surveys done in month 36 and month 48 (Fig. 1).

**Fig. 1 Fig1:**
[figure not shown]
Summary of Project timelines

### Sample size and power calculations

Assuming 32.2% access to services among KP before the intervention in both sites, increasing to 45% in Tanga and 80% in Dar er Salaam city then 250 participants at each site and each time point will give 80% to detect the treatment effect at the 5% level. To account for drop-out and power loss due to the RDS we increase the sample size to 300 per site and per time point.

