### Data management and analysis

#### Quantitative data

A special software package for analysis of RDS data (RDSAT) will be used together with STATA version 15. Because selection probability is not the same for each of the participants when RDS is applied, but larger networks are more likely to be represented than small [26, 27], weighting data based on network size will be done by calculating weight as an inverse of the participant’s network size. The primary outcome variable will be change in the proportion of KP reporting to have accessed services during the period of follow up. Weighted point estimates and 95% confidence intervals (CI) will be calculated. Data will be modelled by multiple regressions including site and time point as well as their interaction as covariates. Generalized estimating equation techniques will be employed accounting for correlation due to repeated measure in the analysis of intervention effectiveness. Cost-effectiveness of intervention will be assessed by calculating incremental cost effectiveness ratio (ICER). All the analysis will be two-tailed and significance level will be set at 5%.

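### The stated 80% power at 250 per site and time point does not follow from the stated access rates, which give more than 99.9%

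*Protocol article*

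**What the plan says.** The section on sample size and power gives three access rates: "Assuming 32.2% access to services among KP before the intervention in both sites", then "increasing to 45% in Tanga and 80% in Dar er Salaam city". From these it concludes: "then 250 participants at each site and each time point will give 80% to detect the treatment effect at the 5% level", which I read as 80% power. The next sentence enlarges the sample: "To account for drop-out and power loss due to the RDS we increase the sample size to 300 per site and per time point". No test, formula, drop-out rate or design effect is given.

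The quantitative analysis section supplies the rest. The model contains site, time point and their interaction, and "All the analysis will be two-tailed and significance level will be set at 5" per cent. The abstract gives the baseline total as "1800 at risk population (900 from Intervention site and 900 from control site". The description of work package 1 explains it as 300 from each of the three key populations in each region, so 300 is the size for one key population at one site and one time point.

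**The concern.** A rise of 12.8 points in one region against 47.8 in the other is a very large contrast. A sample of 250 in each of four cells should detect it almost with certainty, not four times in five. Either an access rate, the comparison or the sample size has been misreported.

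This paragraph is the article's only justification of the trial's size. Someone told 80% would conclude that the study is barely adequate for a 35-point effect and would probably miss anything smaller. That would colour how a modest or null result is read, and the conclusion does not follow from the plan's own inputs.

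**Working it through.** **Inputs.** From the sample-size section: p0 = 0.322 in both regions at baseline; pC = 0.45 (Tanga) and pT = 0.80 (Dar es Salaam) at follow-up; n = 250 per cell; stated power 80%; alpha 0.05. From the quantitative analysis section: two-sided tests and a site-by-time interaction. Four independent cells are assumed, with no design effect at first. The normal-approximation multiplier for 80% power is (1.960 + 0.842)² = 7.849.

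**Trying to reproduce 80% at 250**

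*Risk-difference scale.*
- Effect: (0.80 − 0.322) − (0.45 − 0.322) = 0.35.
- Variance sum: 2(0.322)(0.678) + (0.45)(0.55) + (0.80)(0.20) = 0.4366 + 0.2475 + 0.1600 = 0.8441.
- SE at 250: √(0.8441/250) = 0.0581; z = 0.35/0.0581 = 6.02; power 99.998%.
- n for 80% power: 7.849 × 0.8441/0.35² = 54.1, so 55 per cell.

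*Logit scale.*
- Effect: logit(0.80) − logit(0.45) = 1.587; the baseline logits cancel.
- Variance sum: 2/0.2183 + 1/0.2475 + 1/0.1600 = 19.45.
- SE at 250: √(19.45/250) = 0.279; z = 1.587/0.279 = 5.69; power 99.99%.
- n for 80% power: 7.849 × 19.45/1.587² = 60.6, so 61 per cell.

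A simulation with 200,000 replicates gave power above 99.99% at 250 on both scales.

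**Other readings of the treatment effect.** None gives 80% at 250.
- Follow-up only, 45% against 80%: 29 per group (35 with continuity correction).
- One-sided tests: 43 (risk difference) or 48 (logit).
- 90% power instead of 80%: 73 or 82.
- Alpha divided by three for the three key populations: 73 or 81.
- The 250 split over three key populations (83 each): power is still 93% or 91%.

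**What could lie behind 250.** Three routes come close; the text confirms none of them.
- A design effect already inside the 250: 250/54.1 = 4.6, or 250/60.6 = 4.1. The text, however, makes the RDS allowance afterwards, as 300/250 = 1.2 shared with drop-out.
- A smaller effect: with 62% in Dar es Salaam the difference is 0.17, the variance sum is 0.4366 + 0.2475 + 0.2356 = 0.9197, and n = 7.849 × 0.9197/0.17² = 250.
- A different comparison: the control-region change alone, 32.2% to 45%, needs 226 per time point, or 242 with continuity correction. Power at 250 is 84%, or 81.5% with the correction. This does not use the 80% figure and is not the treatment effect.

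**What 300 per cell offers.** The documents give no design effect, so 1, 2 and 4 are assumptions; no loss is allowed for. The detectable difference solves d = 2.80 × √[(0.4366 + 0.2475 + (0.45 + d)(0.55 − d))/effective n], on the risk-difference scale.

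| Assumed design effect | Effective n | Power for 35 points (risk difference / logit) | Difference detectable with 80% power |
|---|---|---|---|
| 1 | 300 | >99.9% / >99.9% | 15.5 points |
| 2 | 150 | 99.7% / 99.3% | 21.8 points |
| 4 | 75 | 91% / 88% | 30.2 points |

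**The case against.** The best defence is that the error is harmless. It runs towards too much power, baseline collection is complete, and nothing in enrolment, analysis or participant risk changes. That stands as regards severity: this is a reporting correction, not a flaw in the design.

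A second defence is that a condensed article leaves the design effect to the full protocol, where a large RDS allowance might explain 250. The silence on the design effect is indeed no fault in itself. But the article states a definite result from definite inputs, and places the RDS allowance after that result.

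Three stronger readings are tempting and not supported.
- **That the factor of 1.2 is too small and the study is underpowered.** On the stated inputs 300 per cell leaves ample room for RDS; the table shows about 88–91% even at a design effect of 4. Raising n cannot mend a figure whose fault is that it understates power.
- **That 250 must hide a design effect of 4.1–4.6.** A smaller assumed effect or another comparison would give about the same number.
- **That a drop-out allowance is meaningless because follow-up uses new samples.** Work package 3 describes RDS surveys at months 36 and 48, but the analysis section provides for correlation from repeated measures, under which drop-out has a meaning. That is a separate question.

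**Conclusion.** The concern holds as a mismatch between a stated result and its own inputs. The article says 80% power at 250 per site and time point; its rates give more than 99.9%, and 55 to 61 per cell would suffice for 80%. No reading of the stated treatment effect that was tried closes the gap, and the origin of 250 cannot be settled from the document.

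The result assumes independent observations within and between cells and a large-sample test of the interaction. It ignores region-level variation, which cannot be estimated with one region per arm. The table applies to a single key population; it does not describe an analysis pooling all three. Severity is moderate.

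**What to change.** Keep enrolment and rewrite the paragraph.

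1. State the test, the effect and the RDS design effect that produced 250. If one of the access rates or the comparison was misreported, correct it.
2. Restate the power or the detectable difference for 300 per key population, site and time point, naming the scale. Until an estimate is available, label the design effect as assumed and show a range: for 1, 2 and 4 with no loss, 80% power for about 15.5, 22 and 30 points, and power for 35 points of >99.9%, about 99% and about 88–91%. A blanket claim of at least 90% would not hold on the logit scale at a design effect of 4.
3. Replace the assumed design effect with the one estimated from the baseline RDS surveys, which the trial status section reports as complete.
4. Say what loss, if any, the drop-out allowance covers, consistently with how the follow-up samples are drawn.

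The cost is one reworded paragraph and one design-effect estimate from data already collected; no further participants are needed.

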### Description of work packages

#### WP 1: (situational baseline assessment)

Both quantitative and qualitative methodologies will be employed in this work package. In the *quantitative component*, a respondent driven sampling (RDS) methodology will be applied to recruit a total of 300 participants from each of the three KPs in Tanga and Dar es Salaam. RDS is a network sampling methodology designed for hard to reach populations where sampling frames are not available. RDS is a method developed for the sampling from populations for which there is no available sampling frame. The method is based on the principle that initial members of the target population termed as “seeds” refer other members of the same population to participate, so that the sample is established by successive generations of recruitment referrals. RDS builds on a mathematical model which provides a theoretical basis for estimation of population proportions and their variances through statistical adjustment [26, 27] Face to face interviews will be used to collect data on individual, societal and health system push factors (drivers) and pull factors (barriers) associated with the use of general and CHIP services. Data on the challenges and opportunity for integration of CHIPs in the existing health services will be collected. The q*ualitative component* will include use Key Informants Interviews (KII) and in-depth interviews (IDI) to collect information on social connectedness and social support; experience of stigma, denouncement, violence and abuse; and access to and utilization of health services. An ecological theoretical model will be used in analysis of the factors at different levels. During this phase, assessment of structural availability for implementation of KPs intervention will be done.

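### The power section sizes each survey at 300 per site, but baseline is set at 900 per site (300 per key population), so the size of the follow-up surveys and the population of the primary test are not fixed

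*Protocol article*

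**What the plan says.** All references are to the protocol article.

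- **Sample size and power calculations.** The assumptions are "Assuming 32.2% access to services among KP before the intervention in both sites", then "increasing to 45% in Tanga and 80% in Dar er Salaam city". The result is that "250 participants at each site and each time point will give 80% to detect the treatment effect at the 5% level". After an allowance for drop-out and for the sampling method, "we increase the sample size to 300 per site and per time point". Key population is not mentioned as a unit.
- **Abstract, Methods.** "1800 at risk population (900 from Intervention site and 900 from control site) will be recruited at baseline".
- **WP 1 (situational baseline assessment).** The survey will "recruit a total of 300 participants from each of the three KPs in Tanga and Dar es Salaam".
- **Participants recruitment timelines, and WP 3.** Follow-up surveys by respondent-driven sampling (RDS) take place at months 36 and 48. Neither section gives a number of participants.
- **Outcomes.** The primary outcome is the change in the proportion of KP with access to services, over baseline and two follow-ups. It is not stated whether this is one proportion over the three KPs or one for each.
- **Data management and analysis, Quantitative data.** "Data will be modelled by multiple regressions including site and time point as well as their interaction as covariates". No KP term is named.

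**The concern.** Baseline is one of the time points, so the power section and the baseline description should give the same number per site. They give 300 and 900. The follow-up surveys have no size of their own, so anyone planning months 36 and 48 has only the power section to work from, and would recruit 300 per site.

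Two things depend on which reading is right.

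1. **Which test the power statement describes.** If 300 is per KP, the statement describes a test within one KP. If it is per site, it describes a test over all three. The outcome and model descriptions do not settle this.
2. **What happens to KP-specific results.** If each follow-up survey has 300 per site, each KP has about 100 there against 300 at baseline.

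A lesser issue concerns a pooled analysis. Each survey is a new RDS sample. If the KP shares differ between waves in one region and the model ignores KP, the site-by-time estimate can move without any real change in access.

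**Working it through.** **Counts**

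- Baseline: 300 per KP × 3 KPs × 2 sites = 1,800, or 900 per site. This matches the abstract.
- Power section read literally: 300 per site × 2 sites = 600 per survey.
- The two agree only if the 300 in the power section is per KP.
- Interviews over three waves: 1,800 + 600 + 600 = 3,000 if follow-up is 300 per site; 1,800 × 3 = 5,400 if it is 900 per site. The difference is 2,400.

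**Inputs for power**

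From the power section: 32.2% at baseline in both sites, then 45% in Tanga and 80% in Dar es Salaam. The difference-in-differences is (80 − 32.2) − (45 − 32.2) = 35 points. The test is two-sided at 5%. I assume independent samples at each wave. The documents give no design effect (DE), so 1, 2 and 4 are assumptions that show a range.

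**The plan's own figure**

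Sum of the four variances: 2(0.322 × 0.678) + 0.45 × 0.55 + 0.80 × 0.20 = 0.4366 + 0.2475 + 0.1600 = 0.8441.

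n = 0.8441 × (1.96 + 0.8416)² / 0.35² = 54.1, so 55 per site and time point with DE 1 (61 on the log-odds scale). The stated 250 is not reproduced; at 250 the power exceeds 99.9%. A DE of about 4.6 (4.1 on the log-odds scale) would make 250 give 80%, but the text adds its RDS allowance only afterwards, in going from 250 to 300. That is a separate matter. It means, however, that the figure 250 cannot show whether a pooled or a KP-specific test was intended.

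**Power when baseline and follow-up differ in size**

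SE² = DE × [0.4366 / n(baseline) + 0.4075 / n(follow-up)], and power = Φ(0.35 / SE − 1.96).

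*Within one KP, 300 at baseline and 100 at follow-up:* 0.4366/300 + 0.4075/100 = 0.00553, so SE = 0.0744 at DE 1 and 0.35/SE = 4.71.

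- DE 1: Φ(2.75) = 99.7%
- DE 2: Φ(3.33 − 1.96) = 91%
- DE 4: Φ(2.35 − 1.96) = 65%

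*Within one KP, 300 at both waves:* above 99.9%, 99.7% and 91% at DE 1, 2 and 4.

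*Pooled, 900 per site at baseline and 300 at follow-up:* 0.4366/900 + 0.4075/300 = 0.00184, so SE = 0.0429 at DE 1 and 0.35/SE = 8.15. At DE 4, Φ(4.08 − 1.96) = 98%.

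**KP mix, illustration only**

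Assume access of 20%, 32.2% and 44.4% in the three KPs. Equal thirds give 32.2%. A mix of 25/25/50 gives 0.25 × 20 + 0.25 × 32.2 + 0.50 × 44.4 = 35.25%. The pooled figure moves by about 3 points with no real change.

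**The case against.** The strongest reply is that the intent is easy to guess. Because 300 × 3 × 2 = 1,800, the power section most likely means 300 per KP, per site and per time point, and baseline recruitment is already complete. I accept that this is the likely meaning. The text does not say it, though, and for the two follow-up surveys no other passage corrects the literal reading.

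The second reply is that little power is at risk. This largely stands. A pooled test is safe on either reading, and a KP-specific test with 100 per KP at follow-up still exceeds 80% power at design effects of 1 and 2.

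The third reply is that the model sentence is not an exhaustive list, and that stratum terms are commonly left to the analysis plan, which is not shown. This also stands: the absence of a named KP term is a query, not an error. Quotas of 300 per KP in every wave would also fix the unweighted mix.

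A reader might draw four stronger conclusions that the documents do not support.

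- **The trial is underpowered.** The figures above show otherwise for a pooled test.
- **Multiplicity is uncontrolled across three KPs and two follow-ups.** No section plans six such tests; the hypotheses, outcome and model speak of KP collectively.
- **WP 1 may mean 900 in all.** The abstract rules this out with 900 per site.
- **The 1,800 may be 300 × 2 sites × 3 time points.** The abstract assigns 1,800 to baseline alone.

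**Conclusion.** The contradiction is real and lies in the text itself: 300 against 900 per site, a factor of three, in the only statement that sizes the follow-up surveys. It also leaves open whether the power statement and the primary test are pooled or KP-specific.

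The consequence is moderate. Under the stated access rates, the pooled comparison keeps ample power on the literal reading. The cost falls on KP-specific results, where power for 35 points drops below 80% only towards a design effect of 4. These figures rest on the protocol's access rates, independent samples, an equal split of follow-up over KPs, and assumed design effects. The possible bias from a changing KP mix is conditional: it needs a pooled analysis that ignores KP and a mix that shifts differently between regions.

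This should be corrected, but it does not undermine the trial.

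**What to change.** 1. Restate the final sentence of the power section so that it agrees with the abstract and WP 1. If the likely intent is confirmed, it should read 300 per KP, per site and per time point, which is 900 per site.
2. Give the size of the month 36 and month 48 surveys explicitly, per KP and per site.
3. Say whether the power statement and the primary test are KP-specific or pooled.
4. If pooled, include KP as a stratum term in the site-by-time model and average over KPs with weights fixed in advance, so that a change in KP mix between waves cannot appear as an intervention effect. Equal weights are one option; the choice is the sponsor's.

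The cost is wording and one model term. The abstract's 1,800 covers baseline only, so it cannot be cited as already planning 900 per site at follow-up. If the authors meant 300 per site at follow-up, they should keep that size and state that the primary test is pooled and that KP-specific results are less precise, rather than recruit the further 2,400 participants.

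At the time of writing, the article reports baseline as complete and the intervention as still being planned, so these points could be settled before any follow-up data existed.
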